### Safety evaluation and adverse events

Adverse reactions to acupuncture will be evaluated using an adverse reaction assessment form, which includes infections, hematomas, needle syncope, post-needling complications, and other adverse reactions. Throughout the trial, all Serious Adverse Events (SAEs) and Adverse Events (AEs) will be recorded and measured by both the subjects themselves and the acupuncturists. In our trial, SAEs will be defined as events requiring hospitalization, resulting in disability or impaired work capacity, life-threatening conditions, or death. AEs will be classified as treatment-related or non-treatment-related based on their potential correlation with the acupuncture procedure, as determined by the acupuncturist and relevant experts within 24 hours. Given that acupuncture is a minimally invasive treatment, pain that occurs within 30 minutes after needling and resolves spontaneously is not considered an AE due to the inevitable nature of needle-related discomfort. The number of AE cases and treatment sessions will be recorded. We will compare the proportion of subjects who experience treatment-related AEs. Subjects who experience at least one treatment-related adverse reaction will be included in the proportion comparison. If an adverse event is serious and related to this trial, the subject will withdraw from the study and receive appropriate medical care.

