Traditional Chinese medicine offers various SUI treatments, with acupuncture showing the most promising results. A 504-patient RCT found electroacupuncture significantly reduced urine leakage and improved quality of life in middle-aged/elderly women, with clear clinical efficacy and safety [9]. PSUI differs from general SUI, as PSUI is caused by pelvic floor and supporting structure damage from pregnancy/childbirth, while SUI often results from pelvic organ prolapse or muscle weakness. Therefore, the symptoms and treatments for PSUI and SUI are not entirely identical. Previous research has explored acupuncture for PSUI, but evidence on its efficacy is limited [10–12]. High-quality randomized controlled trials are needed to thoroughly evaluate the effectiveness and safety of acupuncture for PSUI treatment. Positive findings could provide a new clinical approach for PSUI while bolstering Traditional Chinese Medicine’s application in modern medicine.

This pilot trial aims to provide evidence that acupuncture has therapeutic effects on PSUI beyond placebo. Prior studies lack sham-controlled acupuncture as a comparator for PSUI [10–12]. To our knowledge, this will be the first acupuncture trial using non-acupoint, shallow, and non-deqi needling as a sham control to rigorously evaluate acupuncture’s efficacy for PSUI. If the true acupuncture group shows superior results, it would preliminarily confirm acupuncture’s therapeutic benefits and inform future formal trials.

The primary objective of this trial is to verify the feasibility of the protocol, defined as meeting the following criteria: (1) dropout rate ≤20%; (2) compliance rate ≥80%; (3) data completeness ≥90%; (4) adverse event rate <5%, with no intervention-related serious adverse events. The secondary objective is to collect preliminary parameters for sample size calculation, including: (1) mean between-group difference in the 1-hour pad test; (2) standard deviation of outcome measurements; (3) estimated effect size (Cohen’s d).

Two hypotheses are proposed: (1) Acupuncture can reduce urine leakage volume in patients with PSUI; (2) Acupuncture is a safe intervention for treating PSUI.

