#### Termination criteria.

(1)At least one urologist or gynecologist must participate in this study. If a patient experiences severe adverse reactions that, in the physician’s judgment, necessitate the termination of their participation in the clinical trial, the case should be withdrawn.(2)If the patient develops other conditions that interfere with trial observations and, in the physician’s judgment, the clinical trial should be terminated, the case will be treated as invalid.(3)If a subject decides during the clinical trial that they no longer wish to participate and requests to withdraw from the study, their request should be respected, and they should be allowed to exit the trial.

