### Allocation

This study will adopt a single-center randomized controlled trial design, randomly allocating 72 eligible patients into the acupuncture group or sham acupuncture group in a 1:1 ratio (36 patients in each group). A completely random digital sequence will be generated by third-party personnel using computer software, without setting any blocking or stratification factors, to ensure a fully randomized allocation process. After obtaining the patient’s informed consent form (**S2 File**), sequentially numbered, opaque, sealed, tamper-resistant, and water-resistant envelopes made of polypropylene (PP) will be utilized. The exterior of the envelopes will be labeled with only the random number and unsealing instructions, while group assignments will be concealed inside the envelopes to ensure allocation concealment. Recruitment personnel will screen and enroll patients who meet the inclusion criteria and distribute the envelopes in order. Before the intervention, the acupuncturist will open the envelope on-site to determine group assignment and administer the corresponding treatment.

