### Blinding

In this trial, blinding will be implemented for participants, outcome assessors, and statistical analysts, with group assignments represented only as A or B. Statistical analysts will conduct the analysis without knowing the actual group assignments, and unblinding will occur only after the statistical analysis is completed. Due to the inherent characteristics of acupuncture, blinding will not be applied to acupuncture practitioners. The roles of acupuncture practitioners, outcome assessors, and statisticians will be carried out by separate individuals to ensure independence and minimize bias. To help maintain participant blinding, adhesive pads will be used in both groups to control for potential biases as much as possible. Unblinding will be permitted only in emergency situations. To assess the success of the blinding process, all participants will be asked to guess whether they received real or sham acupuncture within 5 minutes after their first treatment and again after their final treatment session.

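### The one explicitly defined between-group safety comparison counts only adverse events labelled treatment-related, an unblinded acupuncturist shares in that label, and the Statistical analysis section does not repeat the restriction

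*Protocol article*

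**What the plan says.** **Who knows the arm.** Under Allocation, "the acupuncturist will open the envelope on-site to determine group assignment and administer the corresponding treatment". Under Blinding, "blinding will not be applied to acupuncture practitioners", whereas "blinding will be implemented for participants, outcome assessors, and statistical analysts".

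**Who records and who attributes.** Under Safety evaluation and adverse events, serious and non-serious events "will be recorded and measured by both the subjects themselves and the acupuncturists". Whether an event is treatment-related is then settled "as determined by the acupuncturist and relevant experts within 24 hours". The experts are not identified, and their blinding status is not given.

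**What is compared.** The same section continues: "We will compare the proportion of subjects who experience treatment-related AEs". It then confirms that a subject counts once she has at least one treatment-related reaction. Statistical analysis covers everyone treated at least once. It says adverse event rates will be described and groups compared by chi-square or Fisher's exact test, and does not mention relatedness.

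**What the feasibility verdict uses.** The fourth criterion in the Introduction is "adverse event rate <5%, with no intervention-related serious adverse events". Its first half carries no relatedness condition; its second half does.

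**Who else is available.** Under Termination criteria, "At least one urologist or gynecologist must participate in this study".

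**The concern.** Blinding keeps practitioners apart from outcome assessors to limit bias. For harms, the safety section gives the practitioner part of the assessor's role: the person who opened the envelope and did the needling helps decide whether an event belongs in the numerator.

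The two procedures differ enough for that knowledge to matter. Active needles go in 10 to 40 mm, depending on the point, and are manipulated to obtain deqi. Sham needles stay under 2 mm and avoid it. Someone who knows the arm could judge the same later soreness, dizziness or bruise differently. The direction cannot be predicted. Sham events may be dismissed because the needling was trivial, or active events may be dismissed as an expected part of treatment.

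At stake are the second hypothesis (that acupuncture is safe), the stated between-group comparison, and the zero-tolerance condition on intervention-related serious events, where the label on a single event decides pass or fail.

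**Working it through.** **1. The sections side by side**

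| Place | Endpoint | Depends on the relatedness label? |
|---|---|---|
| Safety evaluation and adverse events | Subjects with at least one treatment-related event, compared by arm | Yes |
| Statistical analysis | Adverse event rates, compared by arm | Not as written |
| Introduction, criterion 4, first half | Adverse event rate below 5% | Not as written |
| Introduction, criterion 4, second half | No intervention-related serious event | Yes |

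The first two rows describe the same comparison differently. Only the first spells out who enters the numerator.

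**2. Inputs for the size of the problem**

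- 36 per arm, 72 in total (Sample size). Exactly 36 treated in each arm is assumed.
- Fisher's exact test when expected counts are small; two-sided, 0.05 (Statistical analysis).
- No event rate or attribution share is given in the document. Those in step 5 are assumptions.

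**3. One relabelled subject**

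If a subject's only related event is relabelled, her arm's rate moves by 1/36 = 2.8 percentage points.

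**4. Effect on the test**

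With equal arms and all events in one arm, the two-sided Fisher p-value is 2 × C(36, k) / C(72, k).

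- k = 6: 2 × 1,947,792 / 156,238,908 = 0.025
- k = 5: 2 × 376,992 / 13,991,544 = 0.054

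Other boundaries, from the full test:

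| Related-event counts | p | One fewer | p |
|---|---|---|---|
| 6 v 0 | 0.025 | 5 v 0 | 0.054 |
| 8 v 1 | 0.028 | 7 v 1 | 0.055 |
| 9 v 2 | 0.046 | 8 v 2 | 0.085 |

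At each boundary, one judgement about one subject changes the reported conclusion. Away from it, relabelling distorts only the estimate: equal counts of 4 v 4 that become 4 v 1 read as 11% v 3%, with p = 0.36.

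**5. Differential attribution over a range of assumptions**

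Labelled rate = true rate × share called related. The chance of p < 0.05 is the sum of Bin(a; 36, p1) × Bin(b; 36, p0) over all pairs (a, b) that Fisher's test rejects.

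| True rate, active v sham | Share called related, active v sham | Labelled rate | Chance of p < 0.05 |
|---|---|---|---|
| 30% v 5% | all v all | 30% v 5% | 0.76 |
| 30% v 5% | 80% v 80% | 24% v 4% | 0.60 |
| 30% v 5% | 50% v 80% | 15% v 4% | 0.18 |
| 30% v 5% | 40% v 80% | 12% v 4% | 0.09 |
| 20% v 20% | 80% v 80% | 16% v 16% | 0.024 |
| 20% v 20% | 80% v 40% | 16% v 8% | 0.091 |

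Unequal labelling can hide a real difference in harms or suggest one that is absent. Equal labelling loses some power but favours neither arm.

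**The case against.** **A reader might infer that the whole safety comparison rests on related events.** The document does not support that. Statistical analysis speaks of adverse event rates and group tests without the restriction, and all events are recorded, so an all-cause table by arm can be produced whatever label is applied. This part of the objection stands: the fault is disagreement between two sections, with the exposed version being the one that is spelled out.

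**A reader might also infer that relabelling could carry the trial past the 5% threshold.** As the Introduction is worded, it cannot, because that half of the criterion is not limited to related events. Only the serious-event half depends on attribution.

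**Nor does the acupuncturist decide alone.** Experts share the decision and blinded participants also record events. This softens the point without removing it. Participants are given no part in attribution, and nothing shows that the experts are masked or have the final say. That an article leaves the experts' blinding unstated is not itself a fault. The fault is that it gives an unblinded role a share in the decision and then builds the comparison on the result.

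**The practical room for bias may be modest.** Several listed reactions, such as hematoma and needle syncope, are plainly procedural. Attribution by the treating practitioner is also a recognisable choice when operators cannot be blinded, and the Discussion concedes that 36 per group may be too few for definitive conclusions. All this limits the expected size. It does not explain why the label should define the main comparison when an all-cause count is already being collected.

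**Conclusion.** The point holds in a limited form. The safety section and the statistics section name different endpoints for the between-group comparison. The endpoint in the safety section, and the serious-event half of criterion 4, depend on a judgement made partly by someone who knows the arm.

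The size that follows from the design is 2.8 percentage points per relabelled subject, with one subject able to cross 0.05 at counts such as 6 v 0. This assumes 36 treated per arm and that the relabelled event is the subject's only related one. The power and error figures rest wholly on assumed event rates and attribution shares. They show the possible direction and scale of distortion and do not predict it. No sample size figure is disputed.

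**What to change.** 1. Align Safety evaluation and adverse events with Statistical analysis: make the main between-group safety comparison the proportion of subjects with any adverse event regardless of attribution, and report treatment-related events as supportive.
2. For the analysis and for criterion 4, have relatedness, including that of serious events, judged from a written description without the arm by the urologist or gynecologist already required, provided that physician has not been told the allocation. The acupuncturist supplies facts only. Participants' clinical care is outside this change.
3. State in the Introduction that the below-5% rate is all-cause, as it already reads.

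**Cost.** Wording changes and a little time from a physician already on the study; no extra patients or staff. Although recruitment had begun, events already recorded can be re-judged masked if this is done before unblinding.

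**Limits.** Some events may reveal the arm by their nature, and the all-cause rate may look slightly less favourable. The change removes attribution from the main comparison but not any influence of the acupuncturist's part in recording events.

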### Data collection and management

The screening phase will last for one week, which includes assessment of basic information such as age, gestational weeks, postpartum weeks, number of pregnancies, and delivery method, as well as detailed information about the subjects’ chief complaints, present illness history, past medical history, family history, and routine physical examination. According to the research protocol, we will collect and record the subjects’ original data completely and truthfully. Any data that significantly deviates from clinically acceptable ranges must be examined and explained. The completed and verified CRFs will be handed over to relevant personnel for data entry, management, and statistical analysis, and the data on the CRFs will not be modified. Any original data will be retained for 5 years after the completion of the study so that readers can access these data by contacting the corresponding author, except for patient identification information.

### Sample size

This study is a pilot trial, and for acupuncture clinical research, a sample size of 30 cases per group in pilot trials is suitable for parameter estimation [17], with a 20% dropout rate taken into consideration. Therefore, this study will enroll 36 subjects per group, for a total of 72 subjects.

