#### Shedding criteria.

Subjects who, despite providing informed consent form and passing the screening process to obtain a randomization number, are unable to complete the treatment regimen and observation period specified in the study protocol are considered shedding cases.

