### Statistical analysis

Statistical analysis will be performed using SPSS software version 26.0. Measurement data will be presented as means and standard deviations (SD) or medians and interquartile ranges (IQR), as appropriate. Counting data will be expressed as percentages.

Efficacy evaluation will adhere to the intention-to-treat (ITT) principle, including all patients who have received at least one treatment. For the primary outcome (1-hour pad test) and secondary outcomes (72-hour bladder diary, ICIQ-SF scores, I-QOL scores, pelvic floor muscle strength test results, and patient self-evaluation of efficacy), a mixed-effects model will be employed to account for the characteristics of repeated measures data. The model will include group, time points, and their interaction as fixed effects, with participants treated as random effects. Baseline values will be incorporated as covariates.

Missing data will be handled using multiple imputation. Five datasets will be generated based on age, sex, body mass index (BMI), baseline characteristics, and outcome values at other time points for analysis. Two sensitivity analyses will be performed for the primary outcome (1-hour pad test): (1) an analysis of the dataset without imputation to assess potential bias introduced by imputation and (2) an analysis of the per-protocol (PP) set to evaluate the impact of adherence. The PP set is defined as participants who completed at least 80% of the planned treatments without significant protocol violations (i.e., at least five treatments in both the acupuncture and sham acupuncture groups).

Safety analysis will include all participants who received at least one treatment. AE rates will be described using counts and percentages. Between-group comparisons will be conducted using the chi-square test when the expected frequency requirements are met; otherwise, Fisher’s exact test will be used. All statistical analyses will be two-tailed, with a significance level of *P *< 0.05 considered statistically significant.

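### The 20% dropout allowance was multiplied on instead of divided out: 36 per group leaves about 29 completers per group, not the 30 cited

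*Protocol article*

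**What the plan says.** The Sample size section rests on a pilot convention taken from a cited source: "a sample size of 30 cases per group in pilot trials is suitable for parameter estimation". It then makes an allowance and draws its conclusion, "with a 20% dropout rate taken into consideration. Therefore, this study will enroll 36 subjects per group", which it totals as 72. The Abstract, Study design, Allocation and Discussion repeat 36 per group or 72 in total and give no other reason for the number.

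Three other places bear on the point.

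- **Who counts as a dropout.** Under Shedding criteria, these are women who have consented, passed screening and received a randomization number, but who "are unable to complete the treatment regimen and observation period specified in the study protocol are considered shedding cases".
- **The feasibility limit.** The Introduction lists "dropout rate ≤20" per cent as the first of four feasibility criteria. The others concern compliance, data completeness and adverse events.
- **What happens to dropouts' data.** Management of shedding cases keeps their data for the intention-to-treat analysis. The Statistical analysis section includes everyone with at least one treatment, uses a repeated-measures mixed model, and adds: "Missing data will be handled using multiple imputation".

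**The concern.** The section presents 36 as what follows from 30 per group once 20% dropout is allowed for. It does not follow. If 20% of those randomized drop out, the number enrolled has to be divided by 0.80, whereas the plan adds 20% of the target. The two operations differ, and the one used always falls short.

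The 30-per-group figure is the only sample-size justification in the document, and at its own assumed dropout the design does not quite deliver it. The trial is also meant to supply data for sizing a formal trial, where the same slip in a larger calculation would carry over. Any reader can check the sentence, so it should be right.

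**Working it through.** **Inputs**

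- Target: n = 30 per group (Sample size).
- Dropout: d = 0.20 (Sample size).
- Enrolled: 36 per group, 72 in total (Sample size, Allocation).
- Denominator of the dropout rate: women with a randomization number (Shedding criteria), so d applies to those enrolled.

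No effect size, standard deviation, alpha or power enters, because the size rests on a convention.

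**1. Reproducing the plan's figure.** n × (1 + d) = 30 × 1.20 = 36. This matches exactly.

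**2. Inflation that keeps 30 completers.** n / (1 − d) = 30 / 0.80 = 37.5, rounded up to 38 per group, 76 in total. Check: 38 × 0.80 = 30.4, whereas 37 × 0.80 = 29.6.

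**3. What 36 delivers.** 36 × 0.80 = 28.8 completers per group; 72 × 0.80 = 57.6 in total, against 60. The gap is 30 − 28.8 = 1.2 completers per group.

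**4. Dropout that 36 can absorb.** 1 − 30/36 = 6/36 = 16.7%.

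**5. Effect on precision.** With d near zero, the approximate 95% half-width for Cohen's d is 1.96 × √(2/n), with n completers per group. The relative standard error of a pooled SD is about 1/√(2(2n − 2)).

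| Completers per group | Half-width for d | Relative SE of SD |
|---|---|---|
| 28.8 | 0.517 | 9.5% |
| 29 | 0.515 | 9.4% |
| 30 | 0.506 | 9.3% |

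**6. Chance of keeping at least 30 completers.** Assume exactly the stated number per arm and independent dropout with probability 0.20, so completers follow Bin(N, 0.80).

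| Enrolled per arm | One arm ≥ 30 | Both arms ≥ 30 |
|---|---|---|
| 36 | 0.401 | 0.401² ≈ 0.16 |
| 38 | 0.655 | 0.655² ≈ 0.43 |

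**7. Against the feasibility limit.** With 72 randomized, 14 dropouts (14/72 = 19.4%) meet the limit and 15 (20.8%) do not. Twelve dropouts (16.7%) leave 60 completers; 13 or 14 leave 59 or 58. A narrow band of results therefore passes on dropout with slightly fewer than 60 completers.

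**The case against.** The case for leaving this alone is that nothing of substance depends on it, and much of that case stands.

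- **30 is not a requirement.** A reader might infer that the design misses a required size. The protocol says only that 30 per group is suitable, as a convention with no power or precision target. Falling to about 29 crosses no threshold fixed in the document.
- **28.8 is not the number analysed.** A reader might infer that only about 29 per group can be evaluated. The plan keeps treated dropouts in the intention-to-treat set, fits a repeated-measures model and imputes missing values. A woman lost after week 2 is a dropout but still contributes her week-2 pad test. The analysed set could reach 36 per arm. This does not rescue the sentence: imputation restores no lost observations, and the plan itself inflated for dropout, which would be pointless if dropouts counted in full.
- **The 16% should not be read alone.** It suggests that the slip causes an 84% chance of falling short in at least one arm. With the correct 38 per arm that chance is still 57%, because inflating to an expected value does not guarantee a minimum. The slip accounts for the difference, about 27 percentage points.
- **The feasibility criterion is not contradicted.** A reader might infer that a pilot could be declared feasible while failing its own size. The Introduction sets no minimum number of completers, so a pilot with dropout at or just under 20% meets that criterion as written.

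The Discussion also concedes that 36 per group may be too few for firm conclusions. That is a fair caution, but it does not correct the arithmetic.

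**Conclusion.** The inflation is wrong as written. The stated inputs, 30 per group and 20% dropout among those randomized, lead to 38 per group (76 in total), not 36 (72). Put the other way, 36 per group goes with about 29 completers per group at 20% dropout, or with a dropout allowance of 16.7%.

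The consequence is modest: about 1.2 completers per group, a half-width for Cohen's d wider by about 0.01, and almost no change in the precision of the SD. The trial's validity and its feasibility criteria are untouched.

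The conclusion rests on reading the 20% as a share of randomized women, which the Shedding criteria support. The completer probabilities further assume exactly 36 or 38 per arm and independent dropout. The precision figures use completers only and an approximation for small effects. The correction is worth making because the error is certain and the remedy is one sentence.

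**What to change.** Keep 36 per group and restate the sentence in the Sample size section along these lines: *36 per group leaves about 29 completers per group at 20% dropout, or 30 at up to 16.7% dropout; with 29 completers per group the 95% half-width for Cohen's d is about 0.515.* Write completers rather than evaluable patients, since treated dropouts remain in the intention-to-treat analysis.

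If the sponsor wants 30 completers per group at 20% dropout to stand, the number that goes with it is 38 per group, 76 in total. The Study status section says recruitment is already under way, and the small gain in precision does not call for that change.

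The cost is one corrected sentence and a slightly less favourable stated figure. No change to the design or the analysis is needed.
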